#### Intervention

The intervention consists of videos being shown in the living room of a residential care facility. In the experimental condition, videos of people walking through different environments are shown; in the control condition, videos of nature and buildings are shown. All videos are made especially for research purposes, and are without sound. There are 10 videos of half an hour each available per condition. For each condition, a compilation of the concerning videos is made, so that the videos can easily be shown successively. The videos are shown on 42 inch Smart TVs. The loop function on these televisions is selected, in order to show the compilation videos continuously. The videos are shown on two television screens per living room, placed in such a way that the videos are visible for all participants from their usual seats. The intervention is an addition to the regular living room setting, that is, if there is already a television present in a living room, that television may stay and the two televisions for the intervention are added.

The intervention has a duration of three months (a recommended minimum duration for physical activity interventions [10]), and takes place five days per week, from Monday to Friday. At the intervention days, the videos should be switched on at the beginning of the day, and switched off at the end of the day. They may also be switched off earlier, if residents move to other rooms earlier during the day.

#### Treatment exposure

In order to know how long the participants were able to watch the videos, the care workers are asked to write down the time the televisions are switched on and off, and, additionally, to write it down if a participant was not present in the living room, for example, due to illness. Caregivers can also write down anything noteworthy about a particular participant, or something more general being observed.

In order to make an estimation of the treatment exposure, observations are being made by the researchers to register how often and how long the participants watch the videos. Per living room, there are three observation shifts during the entire intervention: one from the moment the participants sit in the living room to lunch, one from the start of lunch to diner, and one from the start of diner to the moment the participants have left the living room. The three observation shifts are planned on three separate days.

To determine the total time participants watch the videos, participants’ watching behavior is observed by means of behavior sampling [45]. Each time a participant looks at the screen, the duration of this behavior is written down. However, since multiple participants have to be observed at the same time by one researcher, the observed behavior may be missed at times. For a more detailed observation per participant, each participant is observed individually for one minute per hour, by means of focal sampling [45]. At the start of each hour within an observation shift, all participants are observed successively. Different from the recommended procedure [45], the order in which the participants are observed is kept constant. Similar to the observation order applied in other studies [46,47], the researcher observes the participants starting from the participant sitting most left, continuing towards the participant sitting most right from the researcher.

After a full observation shift, multiple scores of the total time each participant has watched the videos are calculated. The total time is calculated from the behavior sampling procedure and the focal sampling procedure separately, and from the combination of both procedures. The same holds for the number of times each participant has watched the videos. Additionally, the total time the participant is present in the living room during the shift is registered.

#### Measurement occasions

The week before the intervention, baseline measurements take place (T1). The same measurements take place halfway through the intervention, being the seventh week of the intervention (T2), the week immediately after the intervention (T3), and six weeks after T3, during a follow-up week (T4). See Figure 2 for an overview of the complete study period.

**Figure 2 Fig2:**

**Overview of the intervention and measurement occasions.**

During all four measurement occasions, measurements and several test administrations take place (see Table 1). The physical tests are administered by two test administrators and the neuropsychological tests and the QoL questionnaire by one test administrator. All these test administrators are blind to the study condition of the participant.

**Table 1 Tab1:** **Measurements and Test Administrations at T1, T2, T3, and T4 for Participants and Caregivers**

	Participant		
Measures	MMSE 15-25	MMSE <15	Caregiver
**Primary**			
***Physical activity***			
Actometer, worn 24/7 (M10)	X	X	
***Physical performance***			
*Physical functioning*			
TUG (+sensors)	X	X	
4MWS (+sensors)	X	X	
STS	X	X	
*ADL*			
Katz ADL			X
**Secondary**			
***Cognition***			
MMSE	X^a^	X^a^	
8WT	X		
Digit Span	X	X	
VMS	X		
Face recognition	X		
Picture recognition	X		
Picture completion	X	X	
Letter fluency	X		
Category fluency I (animals)	X	X	
Category fluency II (professions)	X	X	
***QoL related***			
*Rest-activity rhythm*			
Actometer, worn 24/7 (IS, IV, RA, M10, L5)	X	X	
*QoL*			
DQoL	X	X	
QUALIDEM			X
*Depression*			
Cornell Scale			X

*Note*. MMSE = Mini-Mental State Examination; M10 = Most active period of 10 hours; TUG = Timed Up and Go test; 4MWS = Four Meter Walking Speed test; STS = Sit to Stand test; ADL = Activities of daily living; 8WT = Eight words test; VMS = Visual Memory Span; QoL = Quality of life; IS = Interdaily Stability; IV = Intradaily Variability; RA = Relative Amplitude; L5 = Least active period of five hours; DQoL = Dementia Quality of Life.

^a^Administration pre-baseline used as score at T1.

The complete neuropsychological test battery including the QoL questionnaire has a duration of approximately 90 minutes. For participants with an MMSE score <15, a shortened neuropsychological test battery is administered in order to still be able to detect possible changes in cognitive functioning, without the need for too much effort of the participant (see Table 1). All other outcome measures are the same for all participants. The shortened neuropsychological test battery including the QoL questionnaire has a duration of approximately 40 minutes. All measurements and tests are described in more detail under the heading ‘Materials’.

### Materials

#### Primary outcome measures

##### Physical activity

Physical activity is measured by means of an actometer, the Actiwatch (AW)2 (Respironics Inc., Murrysville, PA, USA). The actometer has the shape of a watch, and is worn on the wrist of the dominant arm. It is worn 24 hours per day, for a period of seven days. Caregivers are asked to temporarily take off the actometer when a participant takes a shower, goes swimming, or performs another activity in which the actometer could be exposed to too much water.

The actometer measures the arm movements of the participant; based on these movements, the rest-activity rhythm and physical activity are determined. The epoch length used is 1.00 minute. Data are analyzed by means of the PC-program Respironics Actiware 6 (Respironics Inc., Murrysville, PA, USA). Hereafter, five parameters are calculated: Interdaily Stability (IS), Intradaily Variability (IV), activity during the Most active period of 10 hours (M10), activity during the Least active period of five hours (L5), and Relative Amplitude (RA). Additional, more detailed, information on these parameters can be found under the heading ‘Rest-activity rhythm’. The parameter M10 is used to determine the amount of physical activity.

##### Physical performance

Physical functioning To assess physical functioning, three tests are administered. First, the Timed Up and Go test (TUG) [48] is administered. The chair being used for this test should have a seat with a height of 50 centimeters, the seat should be rather hard, and the chair should have armrests. The participant starts sitting in the chair, with his/her back against the backrest. The participant is then asked to stand up from the chair, walk a previously marked distance of three meters, turn around, walk back, and sit down again. The time is measured from the moment the participant starts the test, until his/her back is against the backrest again.

Secondly, the Four Meter Walking Speed test (4MWS) [49,50] is administered, using a slightly adapted protocol (i.e., each of the two conditions of the test is administered once instead of twice). In the first condition of the test, the participant is asked to stand at one spot, and walk a previously marked distance of four meters at his/her preferred speed. In the second condition, the participant is asked to do the same, except now the instruction is to walk the distance as fast as possible. For both conditions, the time it takes the participant to walk the four meters is recorded, as well as the number of steps taken. The mean walking speed and mean number of steps of these two conditions are used as outcome measures.

For these two physical functioning tests, the participants are allowed to use their regular walking aid. Additionally, during the performance of both tests, participants wear two sensors, one attached to the instep of each foot with an elastic strip. The sensors, EXLs1 (EXEL s.r.l., Bologna, Italy), are inertial sensors, equipped with a gyroscope, a magnetometer, and an accelerometer. The data from the sensors is sent to the tablet-PC program μSensorData (EXEL s.r.l., Bologna, Italy) through Bluetooth. For the purpose of the gait patterns analysis, the start and end of each test or condition of the test are marked in the data stream. Gait patterns that can be extracted are velocity and step length. At this moment, it is examined whether it is possible to extract additional gait patterns, such as shuffling gait and wide base.

Lastly, the Sit to Stand test (STS) [51] is administered. The chair being used in this test has to meet the same requirements as the chair being used for the TUG. For the STS, the participant sits down on a chair, and is then asked to stand up and sit down as many times as possible within 30 seconds. Contrary to the original STS, the participant may use his/her arms to stand up and sit down (see also [52]). The total number of times the participant sits down is the score on the test. If a participant ends standing, this counts as an additional half point.

##### Activities of daily living

To assess ADL, the Dutch translation of the Katz ADL [53] is used. This is a questionnaire on how (in)dependent a participant is in the execution of activities of daily life, such as getting dressed. The scale exists of six items which can be scored from 1–3: 1 being completely independent in the activity concerned, and 3 being very dependent. The maximum score on the test is 18, which is indicative of the participant being most dependent. The questionnaire is filled out by a caregiver.

#### Secondary outcome measures

##### Cognition

Global cognition To assess cognition, a neuropsychological test battery is administered. One of the administered neuropsychological tests is the Dutch translation of the MMSE [42]. The MMSE is a test that measures several aspects of cognition, and is therefore used as a test for general cognition. The maximum score on this test is 30, which indicates good cognitive functioning.

##### Short-term memory

The Eight words test (8WT), a subtest from the Amsterdam Dementia Screening test [54], is administered to measure several aspects of memory. First, a list of eight words is read to the participant, and he/she is asked to recall as many of these eight words as possible. The list is then read four more times, and after each time, the participant is again asked to recall as many words as possible, including the words he/she already mentioned in an earlier trial. This subtest, immediate recall, is administered to measure auditory/verbal short-term memory. The score on this test is the total number of correctly recalled words (maximum score: 40).

For the Digit Span test, a subtest of the Wechsler Adult Intelligence Scale III [55], a sequence of digits is read to the participant. In the forward condition of this test, the participant is asked to repeat these digits in the same order. The test starts with two digits in a row, and after three items of the same length, the number of digits increases with one. The largest sequence consists of eight digits in a row. The test is ended earlier if a participant incorrectly repeats at least two items of the same length, but all three items of this length need to be administered. This condition measures auditory/verbal short-term memory. The number of correctly repeated items is the score on this subtest (maximum score: 21).

Finally, also the Dutch version of the Visual Memory Span (VMS), a subtest from the Wechsler Memory Scale [56] is administered. In the forward condition, which measures visual/spatial short-term memory, the participant is shown a card with a pattern of eight squares. He/she is then instructed to tap these squares in the same order as the test administrator demonstrated. The test starts with a sequence of two squares, and after each pair of items of the same length, one square is added. The most difficult sequences contain eight squares in a row. The test is ended earlier if the participant taps both items of the same length incorrectly. The total number of items tapped correctly is the score on this condition (maximum score: 14).

##### Long-term memory

After the immediate recall of the 8WT, there is a delay of about 10–15 minutes in which other, non-memory tests are administered. After this delay, a delayed recall subtest of the 8WT is administered, in which the participant is asked to recall as many words as possible of the eight words mentioned earlier. This subtest measures long-term auditory/verbal long-term memory. The total number of correctly recalled words is the score on this subtest (maximum score: 8).

Following the delayed recall, the recognition subtest of the 8WT is administered, in which the participant is read a list of 16 words. Eight of these words were mentioned earlier, whereas the other eight are new words. The participant has to decide for each word whether it was part of the list mentioned earlier or not. This subtest also measures auditory/verbal long-term memory. The score is the number of correct answers (maximum score: 16).

Two tests of the Rivermead Behavioural Memory Test [57] are administered to measure visual long-term memory. These are Face recognition and Picture recognition. During Face recognition, the participant is shown five cards on which faces are displayed. The participant is instructed to pay close attention, in order to recognize these faces better afterwards. To help the participants pay attention, they are instructed to indicate at each face whether the person displayed is a man or a woman. Each face is shown for five seconds. After a delay of a few minutes, in which a non-memory test is administered, the participant is shown 10 cards with faces. Five of these cards were shown before, whereas the other five were not. The participant is then instructed to say whether the face being displayed is one of the previously shown faces. The score on this test is the number of correct answers minus the number of incorrect answers. The possible scores range from −10 to 10.

The test Picture recognition follows the same protocol as Face recognition, except now first 10 pictures are shown of which the participant has to indicate what the item displayed is. After the delay of a few minutes, in which again a non-memory test is administered, 20 pictures are shown. Of these 20 pictures, 10 were shown before, whereas the other 10 were not. The score is the number of correct answers minus the number of incorrect answers, and ranges from −20 to 20.

##### Visual integration

Picture completion, a subtest from the Groninger Intelligence Test (GIT) [58], is administered to measure visual integration. The participant is shown incomplete pictures, and is asked what is being shown on the picture. If the participant gives an incomplete description, the test administrator asks him/her to describe everything he/she sees. There are 22 pictures in total, of which the first two are examples. The test is ended if the participant has given five wrong answers in a row. The score is the total number of correctly recognized pictures (maximum score: 20).

##### Executive functions: fluency

The Letterfluency test [59] is administered to measure word fluency. In this test, the participant is instructed to name as many words as possible in one minute, all starting with the same letter. He/she is not allowed to say names of people or places, numbers, or successive words starting with the same prefix. First, the participant is asked to name some words with an example starting letter. Then the real test is administered, using the letters ‘D’, ‘A’, and ‘T’. If a participant remains silent for 15–20 seconds, the test administrator helps him/her by giving examples. If necessary due to incorrect answers, instructions may be repeated in between two letters. The score on this test is the sum of the number of correctly named words for each letter.

To measure category fluency, two subtests from the GIT [58] are administered: Category fluency I and Category fluency II. In Category fluency I, the participant is instructed to name as many animals as possible in a period of one minute. The score is the total number of animals mentioned, in which an animal that is mentioned more than once, is counted only once. In Category fluency II, the participant is instructed to name as many professions as possible in one minute. Again, the score is the number of professions mentioned, and the professions mentioned more than once, are counted only once.

##### Executive functions: working memory

The backward condition of the Digit Span test measures auditory/verbal working memory. The protocol for this condition is the same as for the forward condition, except the digits now have to be repeated in reverse order. Again, the number of correctly repeated items is the score on this subtest (maximum score: 21).

The backward condition of the VMS measures visual/spatial working memory. For this condition, the protocol is the same as for the forward condition. The only difference is that the squares now have to be tapped in the reverse order from the order in which the test administrator tapped them. Again, the score is the total number of items tapped correctly (maximum score: 14).

##### Quality of life related factors

Rest-activity rhythm The rest-activity rhythm is measured by means of the actometer, as described earlier in this section under the heading ‘Physical activity’. The above-mentioned five parameters IV, IS, M10, L5, and RA are used to determine the rest-activity rhythm, and will here be described in more detail.

IV is used to determine the rhythm’s fragmentation, thus transitions between activity and rest within 24 hours [60,61]. Scores for IV range from 0 (a little fragmented rhythm) to 2 or higher (a highly fragmented rhythm). IS is used to determine the stability between days [60]: the coupling of the rest-activity rhythm to ‘Zeitgebers’, described by Moore-Ede et al. (as cited in [61]). Scores for IS range from 0 (low stability between days) to 1 (high stability between days), derived from Moore-Ede et al. (as cited in [61]) and elsewhere [60]. M10 is the mean activity during the 10 most active hours during the day, and L5 the mean activity during the five least active hours [61]. RA, the amplitude of the rhythm, is calculated from M10 and L5 [20]. Formulas for IV, IS, and RA can be found elsewhere [60].

##### Quality of life

To assess QoL, two questionnaires are used. One of these questionnaires, the Dutch translation [62] of the Dementia Quality of Life (DQoL) instrument [63], is incorporated in the neuropsychological test battery. The test consists of 29 questions on five different categories of QoL, and one additional question on the participant’s overall QoL. The categories that are measured using the DQoL are self-esteem, positive affect/humor, negative affect, feelings of belonging, and sense of aesthetics. After answering three trial questions, of which the participant needs to answer at least two correct to continue the test, the 30 questions are asked. For all questions, the participant is asked to provide an answer on a 5-point Likert scale. There are three different Likert scales, each used for another selection of questions. As there is a different number of items per above-mentioned category, also the maximum score per category differs [64]. For all categories except negative affect, a higher score means a higher QoL.

The second questionnaire on QoL, the QUALIDEM [65], is filled out by a caregiver. The QUALIDEM consists of 37 questions on nine different categories, and three additional questions for further research [66]. The categories are care relationship, positive affect, negative affect, restless tense behavior, positive self-image, social relations, social isolation, feeling at home, and having something to do. Caregivers can answer the questions on a 4-point Likert scale. As with the DQoL, the number of items per category differs, and therefore also the maximum score per category differs. For each category, a higher score means a higher QoL.

##### Depressive symptoms

To assess the number of depressive symptoms, the Cornell Scale for depression in dementia [67] is filled out by a caregiver [68]. This questionnaire consists of 19 items on five categories: mood related signs, behavioral disturbance, physical signs, cyclic functions, and ideational disturbance. The questions have to be answered on a 4-point Likert scale, of which one option is ‘unable to evaluate’. For this test a total score over all items is calculated. The higher this score, the more depressive symptoms (maximum score: 38).

##### Statistical analysis

First, to compare the two groups regarding participant characteristics, independent sample *t*-tests or Mann–Whitney *U* tests will be used, depending on the distribution, for age, education level, the number of comorbidities, and the number of medicines used. Chi-squared tests will be performed to compare the groups on gender, subtype of dementia, the use of visual, hearing, or walking aids, the presence of (types of) comorbidities, and the use of (types of) medication. If the two groups differ significantly on a participant characteristic, then this variable can be included as a covariate in the hierarchical mixed model analyses.

Group comparisons will also be made for all the baseline values of the physical, cognitive, and QoL related outcome measures, to ensure equality of the groups at the beginning of the intervention. This will be done by means of an independent sample *t*-test or Mann–Whitney *U* test, depending on the distribution.

Hierarchical mixed model analyses will be used to examine the effect of the intervention on primary (physical), and secondary (cognitive, and QoL related) outcomes. For all physical outcome measures (physical activity, the physical functioning tests, the gait patterns, and ADL) mixed models will be fitted with living room as a level 3 variable, participant as a level 2 variable, and, nested within participants, time of measurement as a level 1 variable. Explanatory variables are time of measurement (four levels with baseline as the reference category) and group (experimental and control condition). A significant interaction effect is indicative of a treatment effect.

All the cognitive outcome measures will be transformed into *z*-scores. Then, a factor analysis will be performed in order to examine whether domains can be formed (e.g., a memory domain). A Cronbach’s alpha of α = .70 will be considered sufficient [69]. Subsequently, both for the possible domains, as for the separate neuropsychological tests (using the raw scores for the latter), mixed models will be fitted. The same levels and explanatory variables apply as for the physical outcome measures. Again, a significant interaction effect is indicative of a treatment effect.

For the QoL related outcome measures (the parameters of the rest-activity rhythm, the DQoL, QUALIDEM, and Cornell Scale for depression in dementia), also mixed models will be fitted. Again, the same levels and explanatory variables apply as for the physical outcome measures, and a significant interaction effect is indicative of a treatment effect.

The analyses will be performed on an intention-to-treat basis, using the statistical software PC-program SPSS. For all described analyses, a significance level of α = .05 will be used. The appropriate Bonferroni correction will be applied to the significance level in cases of multiple comparisons within a domain.

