### Power calculation

A power analysis for a 2 x 4 mixed factorial design with two groups and four measurement occasions, with α = .05, β = .80, and an effect size of f(V) = .25, resulted in *n* = 179 participants. Taking into account a dropout of 10%, this results in a total of *n* = 199 participants. This power calculation was performed using G*Power 3.1.4 [44].

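### The treatment effect is an unadjusted difference in change from T1; adjusting for T1 would gain precision, by an amount that depends on a correlation the article does not give

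*Protocol article*

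**What the plan says.** The Statistical analysis section gives the random part of the model: "mixed models will be fitted with living room as a level 3 variable, participant as a level 2 variable". It gives the fixed part as: "Explanatory variables are time of measurement (four levels with baseline as the reference category) and group (experimental and control condition". The result is read as follows: "A significant interaction effect is indicative of a treatment effect". The same levels and explanatory variables are then applied to the cognitive and quality-of-life outcomes.

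The Measurement occasions section places T1 before any exposure to the videos: "The week before the intervention, baseline measurements take place (T1".

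Baseline values of the outcomes are used in only one other way, a t-test or Mann–Whitney comparison between groups. No step follows from the result. The only covariates named are participant characteristics that turn out to differ significantly. No adjustment for the T1 outcome value and no common T1 mean is stated.

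**The concern.** With T1 as the reference level and a free group term, the interaction coefficient for, say, T3 is the T1-to-T3 change in one arm minus that change in the other. The T1 difference between arms enters with weight −1, although its best weight is minus the regression coefficient of follow-up on baseline, which is smaller in size whenever ρ is below 1. Rooms are randomised and T1 precedes the videos, so the two arms have the same expected T1 mean. The model does not use that information.

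What is at stake is precision on every outcome, primary and secondary, from data the trial collects anyway. Testing baseline values for significance does not help: it neither makes the arms equal nor changes the estimator.

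**Working it through.** **1. The plan's own sample size.** The Power calculation section uses a two-by-four repeated-measures layout. Its settings are: "with α = .05, β = .80, and an effect size of f(V) = .25". Reading the printed β as power, and taking the multivariate within-between interaction test with df1 = (2−1)(4−1) = 3, df2 = N−4 and noncentrality N × .25², the smallest N reaching 80% is 179 (power .8015). With 10% dropout, 179/.90 = 198.9, so 199. Both figures reproduce. The sample size therefore rests on a joint 3-df test, and any gain has to be stated for that test as well as for a single contrast.

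**2. Inputs not in the article.** It gives no correlation between occasions, no standard deviation, no intraclass correlation and no number of living rooms. Everything below depends on an assumed ρ, equal between all pairs of occasions.

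**3. Single contrast (T1 to one later occasion), no clustering.** Per-participant variances:
- change: 2σ²(1−ρ)
- adjusted for T1: σ²(1−ρ²)
- ratio: (1+ρ)/2, so the saving is (1−ρ)/2

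For ρ = .7 the ratio is 1.7/2 = .85, a saving of 15%.

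**4. Single contrast with clustering.** Generalised least squares was applied to the three-level model with the T1 group difference free, then fixed at zero. The assumed values were a room intraclass correlation of 0 to .10, 2 to 10 participants per room, and a room-by-time variance of 0 to .02 of the total.

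**5. Joint 3-df test, no clustering.** Given T1, the covariance of T2–T4 is proportional to I + ρJ; for changes from T1 it is proportional to I + J, with the same factor (1−ρ). The ratio of required sample sizes is then:
- effect equal at T2–T4: (1+3ρ)/4
- effect at one occasion only: .75(1+3ρ)/(1+2ρ)

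At ρ = .6 these are 2.8/4 = .70 and .75 × 2.8/2.2 = .955.

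| Assumed ρ | Single contrast | Single contrast, clustered | Joint test, equal effect (N instead of 179) | Joint test, one occasion (N instead of 179) |
|---|---|---|---|---|
| .5 | 25% | 13.2–28.8% | 37.5% (114) | 6.25% (168) |
| .6 | 20% | 10.5–24.6% | 30% (127) | 4.5% (171) |
| .7 | 15% | 7.9–20.3% | 22.5% (140) | 3.1% (173) |
| .8 | 10% | 5.3–16.1% | 15% (153) | 1.9% (176) |
| .9 | 5% | 2.6–11.9% | 7.5% (166) | 0.9% (177) |

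**6. Effect of a chance T1 difference.** If the arms happen to differ by d at T1, the expected follow-up difference is the true effect plus ρd (no clustering). Subtracting d leaves the true effect minus (1−ρ)d. Over repeated randomisations d averages zero, so there is no bias overall.

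**The case against.** The strongest reply is that the planned interaction is a standard estimator, unbiased under randomisation, with its type I error intact. That stands: this is a loss of efficiency, and the section contradicts nothing.

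A second reply is that the gain may be small for the test the trial was sized on. That also stands: if the effect appears at one occasion only, the joint test saves about 2% to 5% at ρ of .8 to .6.

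A third is that forcing equal T1 means is safe only if allocation cannot influence who is enrolled. The same researcher includes rooms and draws the lots, and under the Study design section some single rooms are assigned without a draw. The Inclusion of participants section has at least two residents agree before a room can enter. The article does not say, however, whether all enrolment and T1 measurement precede the room's allocation. This bears mainly on the common-mean version; using T1 as a covariate largely meets it.

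A reader might also infer that imbalance is likely because there are few living rooms. The article gives no number of rooms: it sets a target of 199 participants and a minimum of two per room, which leaves the number open.

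**Conclusion.** The point holds as a matter of efficiency. T1 is a free outcome level in each arm, the effect is an unadjusted difference in change, and the baseline significance tests do not remedy this. Under the assumptions above, the saving is positive for any ρ below 1.

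Its size cannot be fixed from the article. For one contrast it is about 5% to 25% (ρ of .9 to .5, no clustering), or about 3% to 29% under the assumed clustering values. For the joint 3-df test at ρ of .8 to .6 it is about 15% to 30% with an equal effect at T2–T4 and about 2% to 5% with an effect at one occasion.

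Two stronger readings are tempting. One is that change from T1 biases the result. It does not under randomisation; the shift of (1−ρ)d exists only conditional on an observed T1 difference. The other is a single headline gain of 10% to 20%. That range needs ρ of .6 to .8, which the documents do not give, and it describes one contrast without clustering rather than the planned interaction test.

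**What to change.** For every outcome, model T2–T4 with T1 and T1-by-time as covariates, keeping the living-room and participant levels, and test group and group-by-time together. The sentence that equates a significant interaction with a treatment effect must change with it: once T1 leaves the outcome vector, the interaction alone shows only whether the effect varies over T2–T4.

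Alternatively, if residents are enrolled and T1 is measured before the room's allocation can influence them, keep T1 in the outcome vector with a common mean in both arms: time plus group-by-T2, T3 and T4, with no group main effect. State the order of enrolment, T1 and allocation in support. The clustered range above was computed for this version; without clustering the two versions give the same saving.

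The cost is one changed model specification and no new data. The covariate version needs a simple rule for missing T1 values. The common-mean version relies on allocation not influencing enrolment.
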